#### Diagnostic interview study

This study will validate the screening questionnaires used for general distress and PTSDs using diagnostic interviews with the CIS-R and the CAPS-5, respectively. Participants for the validation studies will be randomly selected from those with non-missing screening scores in a 50% ratio of caseness or otherwise. Sample sizes were obtained by simulation studies (n=250 and 100, respectively, for the CIS-R and CAPS-5 diagnostic interviews). Sensitivity, specificity, and positive and negative predictive values will be calculated. If possible, prevalence values for the population at risk will be calculated using population weightings (which will be derived from sex, age and ethnicity variables in an attempt to ensure representativeness in the sample population). Sensitivity analyses will be undertaken to account for missingness if necessary.

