#### Diagnostic interview study

Participants will be up to 350 HCWs who have completed the baseline NHS CHECK survey.

Up to 250 participants will be purposively sampled according to their responses to the General Health Questionnaire (GHQ) in the short survey module;^13^ half will meet caseness and half will not meet caseness. These participants will be administered the Clinical Interview Schedule-Revised (CIS-R).^14^ The number of CIS-R interviews (n=250) has been chosen balancing precision and cost. Based on a simulation study, we anticipate that 250 interviews will allow estimation of CIS-R prevalence of common mental disorders to within ±6%.

Up to 100 HCWs will be sampled according to their responses to the 6-item PTSD Checklist civilian version (PCL-6)^15^ in the long survey module; half will meet caseness and half will not meet caseness. These participants will be administered the Clinician-administered PTSD Scale (CAPS-5).^16^ This sample size was calculated as the necessary number to achieve a valid estimation of PTSD prevalence.

Sampling for the CIS-R and CAPS-5 groups will be stratified to ensure representation from each of the 18 participating sites in the NHS CHECK Study, as well as to ensure ethnic, sex and age breakdown that resembles respondents of the baseline survey.

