### Analysis plan

#### Longitudinal cohort study

Response weights will be calculated for each Trust, generated using a raking algorithm based on age, sex, ethnicity and role (using Trust population data obtained from Human Resources), with missing demographic data imputed using multiple imputation (for the purposes of weighting only). Trusts with response rates under 5% will be dropped from the analysis. Representativeness of the sample will be described using frequencies and percentages, and descriptive statistics given for each variable to summarise participants (frequencies and weighted percentages for categorical variables, mean and SD for continuous variables). We will examine differences between participants completing only the short survey, compared with those completing both the short and long surveys. We will summarise the weighted prevalence of the primary and secondary outcomes, stratified by sociodemographic and occupational factors. We will explore potential longitudinal associations between sociodemographic characteristics and occupational factors with the outcome measures (eg, GHQ-12, GAD-7, PHQ-9, AUDIT, PCL-6, MIES). Three-level random intercept linear or logistic (depending on the distribution of the outcome) regression models will be used to account for the hierarchical structure of the data, considering observations from baseline, 6-month follow-up and 12-month follow-up at level 2 and NHS trusts at level 3. We will use a measure of pressure on Trusts as the key exposure (eg, ratio of beds in use to staff numbers, ie, those not on sick leave), plotting levels of this exposure over time (aggregated at the Trust level), before partitioning the data into meaningful periods corresponding to burden level over the baseline data collection period (April 2020 to January 2021). We will plot all measures over time to look at patterns between this exposure and outcome levels, and use three-level random intercept logistic and linear regression models, as appropriate, to explore factors associated with outcomes in each period.

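### Both diagnostic interview samples are split 50:50 on screen status, but the stated prevalence weights omit screen status and none are stated for sensitivity and specificity, so all three miss their population values unless caseness is 50%

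*Protocol article*

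**What the plan says.** The sample description for the diagnostic interview study (Study population and sample) fixes the split for both instruments: "half will meet caseness and half will not meet caseness". The analysis plan for the same component repeats it: "Participants for the validation studies will be randomly selected from those with non-missing screening scores in a 50% ratio of caseness or otherwise". The sizes are "n=250 and 100, respectively, for the CIS-R and CAPS-5 diagnostic interviews". The sample description also stratifies interviewees so that their ethnicity, sex and age resemble those of baseline respondents.

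In the analysis plan, prevalence is to be calculated, if feasible, with "population weightings (which will be derived from sex, age and ethnicity variables in an attempt to ensure representativeness in the sample population". On accuracy it says only: "Sensitivity, specificity, and positive and negative predictive values will be calculated". The cohort weights are described separately as "generated using a raking algorithm based on age, sex, ethnicity and role".

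Two further statements bear on the selection:

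- The sample description says "Up to 250 participants will be purposively sampled according to their responses to the General Health Questionnaire (GHQ", whereas the analysis plan describes random selection.
- The inclusion criteria for this component list a GHQ score of 4 or more, or a PCL-6 score of 14 or more, as something participants must have.

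Establishing the true prevalence of disorders is part of the primary objective (Aims, objectives and hypotheses).

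**The concern.** This is a two-phase design in which the chance of being interviewed depends on the screening result. Any quantity that averages over screen-positives and screen-negatives needs each stratum returned to its share of the population. Prevalence, sensitivity and specificity are all of that kind. PPV and NPV are conditional on the screen result and are not.

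The listed variables cannot do this job. Interviewees are already stratified to resemble baseline respondents on ethnicity, sex and age, so weighting on those variables leaves the sample close to half screen-positive.

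At stake is the study's main claim for this component. The Introduction argues that questionnaires overestimate prevalence and that interviews will correct this. If caseness is below 50%, the weights as written bring an overestimate back.

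**Working it through.** **Inputs from the article.** Half of each sample is screen-positive (125 and 125 for the CIS-R; 50 and 50 for the CAPS-5). The weighting variables are sex, age and ethnicity. CIS-R precision is stated as "we anticipate that 250 interviews will allow estimation of CIS-R prevalence of common mental disorders to within ±6" percent.

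**Inputs not in the article, so assumed.** Cohort caseness w; disorder rate a among screen-positives; disorder rate b among screen-negatives.

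**The plan's own figure.** The inputs to the ±6% simulation are not given, so it cannot be strictly reproduced, but it is plausible. At 95% confidence, a simple random sample of 250 gives 1.96 × √(0.25/250) = ±6.2 points at worst and 1.96 × √(0.3 × 0.7/250) = ±5.7 points at 30% prevalence. A screen-weighted estimator has half-width 1.96 × √[w²a(1−a)/125 + (1−w)²b(1−b)/125]. This runs from ±3.6 to ±6.5 points for w from 0.30 to 0.70, a from 0.3 to 0.6 and b from 0.05 to 0.2. The ±6% is not the problem.

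**Formulas.**

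- Prevalence: target wa + (1−w)b; at 50:50, (a+b)/2. The difference is (0.5−w)(a−b), which is zero at w = 0.5 and changes sign there.
- Sensitivity: target wa/prevalence; at 50:50, a/(a+b).
- Specificity: target (1−w)(1−b)/(1−prevalence); at 50:50, (1−b)/(2−a−b).

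**Illustration.** PTSD uses a = 0.30, b = 0.03; CIS-R uses a = 0.35, b = 0.10.

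| | w | Prevalence: target vs 50:50 | Sensitivity | Specificity |
|---|---|---|---|---|
| PTSD | 0.15 | 7.05% vs 16.5% | 64% vs 91% | 89% vs 58% |
| PTSD | 0.35 | 12.45% vs 16.5% | 84% vs 91% | 72% vs 58% |
| CIS-R | 0.40 | 20% vs 22.5% | 70% vs 78% | 67.5% vs 58% |
| CIS-R | 0.60 | 25% vs 22.5% | 84% vs 78% | 48% vs 58% |

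For example, PTSD at w = 0.15: 0.15 × 0.30 + 0.85 × 0.03 = 0.0705, against (0.30 + 0.03)/2 = 0.165.

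**Can demographic weights rescue it?** A simulation of 4,000 replicates weighted either on one demographic variable associated with screening positive or on screen status.

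- CAPS-5 (w = 0.2125, a = 0.30, b = 0.02): the truth is 8.0%. Demographic weighting gave 15.7%, or 16.0% when the sample already matched on the demographic. Screen weighting gave 7.9%.
- CIS-R (w = 0.375, a = 0.50, b = 0.10): the truth is 25.0%. Demographic weighting gave 29.9% and screen weighting 25.0%.

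**Effect on precision.** With the PTSD inputs above and 50 per stratum, the 50:50 estimate has half-width 1.96 × √(0.25 × 0.21/50 + 0.25 × 0.0291/50) = ±6.8 points. Screen weighting gives ±4.5 points at w = 0.15 and ±5.4 at w = 0.35, before any weights for participation.

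**The case against.** The article is condensed. It does not say that the two strata will be pooled at 50:50, and a correct prevalence could be assembled from outputs it does plan: predictive values from the interviews and weighted caseness from the cohort. That is true, but the article does name the weighting variables, and the one that governs selection is absent. This is a choice written down, not a detail left out.

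The objection limits the point in four ways.

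- A reader might infer that the estimates are certain to be biased, or always too high. They are not: the error is zero at 50% caseness and reverses above it.
- A reader might infer that PTSD is worst affected. No caseness rate for either screen is given, so that ranking rests wholly on assuming that PCL-6 caseness lies further from 50% than GHQ caseness.
- A reader might blame the demographic weights for the error in sensitivity and specificity. The weighting sentence covers prevalence only; for the accuracy measures the point is that no weighting is stated.
- The same screens are given again 1 to 3 days before the interview, and the analysis plan does not say which administration is the index test. The statement that predictive values are unaffected, and the formulas above, hold for baseline screen status.

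Leaving role out of the interview weights could be defended as parsimony with 250 and 100 interviews, and the point does not rest on it. The purposive wording can be read as deliberate stratification on the GHQ with random choice inside each stratum; if that is meant, the text should say so.

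**Conclusion.** The concern holds in conditional form. As written, the analysis does not return the screen strata to their population shares, so prevalence (part of the primary objective), sensitivity and specificity are off target unless caseness happens to be 50%. The prevalence error is (0.5−w)(a−b). Under the stated assumptions that is 4.05 to 9.45 points for PTSD, and at most 2.5 points in either direction for the CIS-R, which is inside the stated ±6%. The direction of the mechanism follows from the design, given more disorder among screen-positives than screen-negatives. The sizes are illustrations, since the article gives no caseness rates or disorder rates by screen status.

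Separately, the inclusion criteria conflict with the sampling scheme. Read literally for each instrument, they admit no screen-negatives, which would leave sensitivity, specificity and NPV inestimable and nothing to weight back.

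**What to change.** In the analysis plan for the diagnostic interview study:

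1. Add to the weights the inverse probability of selection by baseline screen stratum. For the CAPS-5, also account for completion of the optional long survey, where the PCL-6 sits.
2. Combine this with the cohort population weights.
3. Apply the combined weight to prevalence, sensitivity and specificity, and use stratified (two-phase) standard errors.

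Elsewhere, reconcile purposive sampling in the sample description with random selection in the analysis plan, because the weights need known selection probabilities. Also reconcile the caseness criterion in the inclusion criteria with the half of each sample meant to fall below the cut-off.

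The cost is wording and analysis code, using baseline screen scores already held; no further interviews are needed. Screen weighting need not cost precision: in the PTSD illustration it narrows the interval, although participation weights could offset some of that.

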#### Qualitative interview study

Interviews will be audio-recorded and transcribed verbatim with identifying information removed. Transcripts will be pseudo-anonymised and uploaded to Nvivo V.12 for windows. An inductive qualitative methodology will be used to analyse the interviews underpinned by a pragmatic approach to inquiry. The principles of reflexive thematic analysis will be used to allow an open and organic coding process to develop.^27^ Themes will be developed in an iterative process after the initial stages of coding by considering the differences and similarities in the experiences and views of participants from each of the different groups. An initial inductive approach will be applied, more to a more deductive approach over time. A collaborative coding process will be employed, in which members of the research team will initially independently code transcripts and generate a coding framework through discussion. To enhance validity, the emerging thematic framework will be discussed with the wider research team and will be member-checked with several interviewees who consented to be contacted again for this purpose at interview.

### Patient and public involvement

Front-line NHS staff working in intensive care environments proposed this research, having identified a need to rapidly understand and intervene to try and ameliorate the impact of the pandemic on staff. We tested the proposal’s acceptability and approach with a small informal reference group of front-line staff (psychologists, managers, intensivists and trainee psychiatrists) and refined it accordingly. We have developed an online advisory group of NHS staff (clinical, managerial, auxiliary, students) and NHS patients to provide input on methods development, recruitment strategy, communications and interpretation of findings. We will also consult this group on tasks such as developing brief lay summaries and interview schedules. We will also run a social media campaign on twitter to raise awareness of the study, as well as to help disseminate our aims, work and results while restrictions on face-to-face events are in place. This will be accompanied by a poster campaign to raise awareness, and increase recruitment to the study, with posters being displayed in sites across all the trusts in the study.

## Ethical considerations

### Longitudinal cohort study

Once consented into the study, an automatically assigned ID number will be used for each participant, allowing survey data to be held pseudonymously. All study staff will adhere to relevant data protection regulations, and will maintain confidentiality at all times. No information that could identify any individual participant will be used in reports or publications, or passed on to the Trusts.

Participants will be able to stop the survey at any point, and can skip questions wherever desired. The only required questions are email address and main employing Trust. Signposting information will be provided for any participants who experience distress in answering survey questions (eg, links to websites for NHS front-line staff, Mind, Samaritans and the WHO resources for dealing with psychosocial considerations during the pandemic).

There might be some indirect benefits to the participant when taking part. People often value the opportunity to share their opinions, experiences and feelings, and several free-text options throughout the surveys offer the chance to do this.

### Diagnostic interview study

Participants will be asked to discuss their mental health, which can sometimes cause distress. Participants can stop interviews at any point for a break, postpone the interview to another time or day, or end the interview completely. The researcher will provide immediate emotional support, offer to pause or postpone the interview, and offer to contact a friend, family member or other supportive person for participants who show signs of distress. The same signposting information outlined above will be provided to any participants who request this. The research team does not take clinical responsibility for research participants in this study; this is made clear during the consent process. However, a standard risk protocol with a supervising clinician will be followed for participants who indicate that they are at risk of harming themselves or others at any stage of the recruitment or participation process.

As with the survey, there may be some benefits to taking part. People often find it helpful talking about their own experiences. The information gained from the study will be used to inform immediate and future responses to the pandemic, and some people enjoy knowing that they have contributed to this.

### Qualitative interview study

Despite the focus of the interview being on evaluating staff supports, some participants may experience distress in answering questions that draw on their experiences of the COVID-19 pandemic. The nature of the interview will be carefully explained in the PIS and the consent form. Participants will be able to pause the interview at any time, skip any questions and stop the interview entirely, or ask the interviewer to resume another day (this will be arranged wherever possible). Information will be made available at the end of the interview, and after more sensitive questions, for participants who recognise that they are feeling distressed. This will include resources signposting people to support services and helplines. The same risk protocol as above will be followed.

There might be some indirect benefits to the participant when taking part. People often value the opportunity to discuss their experiences and feelings. Further, people may feel keen to contribute to research concerning such a stressful and unprecedented situation. Various members of the research team have been running studies into mental health and well-being for many years, including many tens of thousands of participants, and distress resulting from answering questions like the ones proposed in the current study is extremely rare.

## Dissemination

We aim to rapidly disseminate summary findings to the senior management of participating Trusts and collaborating organisations such as NHS England in order to inform staff health and well-being strategies. Findings will be more broadly disseminated within the Trusts through their communication channels including websites and staff newsletters. Research findings will also be disseminated to NHS Trusts nationally via our professional network and professional bodies. In addition, findings will be published in academic journals, at conferences and stakeholder meetings and summaries placed on the dedicated study website.
